#### Secondary outcome: physical fitness measures

The fitness outcome measures involve the measures of height, weight, body composition, and senior physical fitness test battery [35]. Four senior physical fitness tests including seat-chair stand, arm curl, 2-min step test, and 8-feet up-&-go will be adopted except for back scratch and chair sit-&-reach. Flexibility will not be tested because both CCPT and physical training programs are not designed for flexibility training. One additional test of the ‘four-square step test’ on dynamic balance assessment [36] will be taken because CCPT and physical training programs involve balance training. In particular, the Line dancing routines involve many walking and body turning movements, which require dynamic balance. All the selected tests have been previously found good reliability and validity when testing older adults [35]. These five tests have been used to assess fitness and balance functions in cognitive or exercise intervention studies [37–39]. The functional fitness norms have been established for community-dwelling older adults in Hong Kong [40].

#### Other pre-specified outcomes: psycho-social-related measures

Scales of behavior changes, intention/motivation, physical activities, loneliness physical health, infection with coronavirus, and subjective health status will be measured in one survey (see Additional file 4). The Centre for Epidemiological Studies-Depression (CES-D) will be used to measure how often over the past week the participants experienced symptoms associated with depression, such as poor appetite, feeling lonely, and restless sheep [41]. The score of CES-D is the sum of the 20-items with a possible range of 0 to 60 in total. The scoring of positive items is reversed, which means the higher scores indicate the presence of more symptomatology. The participants who obtain a score of 16 or greater are considered at risk of depression. If more than 4 questions have missing answers, the score of CES-D will not be marked. All the questionnaires are administered using the Qualtrics system.

### Statistical analysis plan

Data analysis will be performed using the Statistical Package for social sciences (IBM SPSS ver. 27). All data points that were considered outliers, which are out of the interquartile range (IQR) covering the 50% central of samples, will be excluded from analyses. For analyzing program effects, a mixed-effects ANOVA will be used. In this model, there will be a between-subjects factor consisting of five groups (CGs = 0, IGs = 1 to 4) and a within-subject factor consisting of four Trials (Time = 1 to 4). The dependent variables will be the outcome measures of the three cognitive tests and the five physical fitness tests. The independent variables will be time (1 pre-test, 2 post-tests, and 1 follow-up) and intervention (IGs with 4 combinations of training modes & CGs). The participating elderly centre as a cluster will be treated as a random effect. Assumptions (normality, sphericity, etc.) for mixed-effects ANOVA will be tested using an alpha level set as 0.05. The focus of this mixed-effects ANOVA will be mainly on the between-group differences, i.e., the differences among the four IGs. Post-hoc comparisons among IGs will be conducted with Bonferroni correction after finding significant effects. Next, for analyzing specific intervention effects in the 3 treatments crossover design, a similar mixed-effects ANOVA will be used. In this second model, there will be one within-subject factor of four repeated trials (Time = 1 to 4). The dependent variables will be the outcome measures of the three cognitive tests and the four physical fitness tests. The independent variables of time (pre-test, 2 post-tests, and follow-up) and three training modes will be examined by ANOVA with repeated measures. The focus of the second model is to examine the individual effect of the three training modes, so a pre-planned contrast will be conducted to examine their effects. Based on these statistical analyses, results and conclusions will be drawn.

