### Sample size

As suggested by Brown et al. (2015) [20], the first step of CRCT sample size estimation is to determine one for a non-clustered design. Based on the repeated measures of ANOVA analyses of 4 trials by 5 groupings (4 IGs + 1 CG) with parameters set to an effect size of 0.175 (small to medium), an alpha level of 0.05, power of 0.90, rho of 0.5, the sample size (*n*_*n*_) estimated is 95 (calculated by G*Power software). Next, the second step is to determine the design effect (*D*_*e*_) for clustering estimation. It is calculated with a group size of 15 and ICC of 0.1 (from previous a study titled BIGMAP, to be published) [15] and yields 2.4. The required sample size for a CRCT is 228 (i.e., *n*_*n*_×*D*_*e*_). By considering a 20% of attrition rate of the participants, the total sample size (*N*) of this study is set at 285, composed of 20 groups/centres of 14–15 participants each.

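### The outlier rule as written excludes every value outside the interquartile range, which is half of the valid outcome data

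*Protocol article*

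**What the plan says.** The rule stands near the start of the Statistical analysis plan section, ahead of both ANOVA models. It covers "All data points that were considered outliers" and defines them as those "which are out of the interquartile range (IQR) covering the 50% central of samples, will be excluded from analyses". The section gives no multiplier or fence, no check against source and no analysis without the exclusion. It does not say whether quartiles are taken over all arms, within arm or by visit.

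The dependent variables that follow are the three cognitive tests (the primary outcome) and the physical fitness tests, each at four assessments.

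The Sample size section assumes a repeated-measures ANOVA with "an effect size of 0.175 (small to medium"), "an alpha level of 0.05" and "power of 0.90, rho of 0.5". Its only allowance for lost data is 20% attrition.

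**The concern.** The interquartile range holds the middle half of any sample, so a rule that drops everything outside it drops about half of perfectly good data. The words about the central 50% confirm that the quartiles themselves are the cut-points.

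This is a selection on an outcome measured after randomisation. High and low scores go because they are high or low, not because they are wrong. The harm depends on how the quartiles are computed:

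- **Pooled over arms:** all arms are cut to the same narrow window, so their means are pulled together and a real effect nearly vanishes.
- **Within arm:** the difference in means survives, but the spread is artificially small. Standard errors are then too small and false positives multiply.

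In either case the 90% planned power no longer describes the analysis, and the rule reaches every primary and fitness result.

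**Working it through.** **1. The plan's own sample size.** Inputs from the Sample size section: 4 trials, 5 groups, effect size 0.175 (read as Cohen's f), alpha 0.05, power 0.90, rho 0.5, group size 15, ICC 0.1, attrition 20%.

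- Group-by-time F test with λ = f²·N·m/(1 − rho), df1 = (5 − 1)(4 − 1) = 12 and df2 = (N − 5)·3. With equal groups, N = 95 gives power 0.909, matching the stated 95.
- Design effect = 1 + (15 − 1) × 0.1 = 2.4.
- 95 × 2.4 = 228, and 228 / 0.8 = 285.

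The stated figures reproduce. The fault is in the analysis rule, not in this arithmetic.

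**2. Values lost.** By definition 50% per outcome (slightly less if scores are tied). For normal data with quartiles taken at each visit (±0.674 SD):

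| rho | inside at all four visits | inside at both T1 and T3 | inside at no visit |
|---|---|---|---|
| 0.3 | 7.3% | 26% | 7.9% |
| 0.5 (protocol) | 9.5% | 28% | 11.4% |
| 0.7 | 14.5% | 31% | 18.0% |

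At rho 0.5, 0.095 × 285 ≈ 27 participants are complete, or 0.095 × 228 ≈ 22 after the planned attrition.

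**3. Spread retained.** The variance of a normal variable cut at its quartiles is 1 − 2zφ(z)/0.5. With z = 0.674 and φ(z) = 0.318 this is 0.143, so the SD is √0.143 = 0.38 of the original.

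**4. Two arms, one visit, t-test.** Simulation with 285 / 5 = 57 per arm, no clustering and no attrition. The 0.5 SD effect is illustrative and not from the protocol.

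| Rule | Power at 0.5 SD |
|---|---|
| No exclusion | 76% |
| 1.5 x IQR fence | 73% |
| Outside IQR, pooled quartiles | 11% (mean estimate 0.08 SD) |

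With no true difference and within-arm quartiles, the type I error is 30%. An analytic check agrees. The naive standard error uses SD 0.378 and half the sample, so it is 0.378/√0.5 = 0.534 of the full-data standard error. Under normality a mean of the middle half cannot be more precise than the full mean, so the true standard error is at least 1. The large-sample type I error is therefore at least 2 × [1 − Φ(1.96 × 0.534)] ≈ 0.295.

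**5. Five groups, four visits, group-by-time test.** Simulation using all available data, 228 / 5 ≈ 46 per group, rho 0.5, no clustering. The effect is a gain of 0.5 SD in every intervention group from T2 onwards.

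| Rule | Type I error | Rejection rate with effect |
|---|---|---|
| No exclusion | 0.05 | 0.68 |
| 1.5 x IQR fence | 0.05 | 0.64 |
| Outside IQR, pooled quartiles | 0.05 | 0.08 |
| Outside IQR, within-group quartiles | 0.59 | 0.93, not interpretable as power |

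**6. Most lenient view.** Suppose the loss were random and simply halved the sample. Then 228 becomes 114, the cluster size is 114 / 20 = 5.7, the design effect is 1 + 4.7 × 0.1 = 1.47, and the effective N is 114 / 1.47 ≈ 78. Power falls from 0.91 to about 0.82. This understates the harm, because the loss depends on the outcome.

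**The case against.** The strongest reply is that this is a drafting slip. The sentence speaks of outliers, the sample size allows for nothing beyond 20% attrition, and no investigator plans to discard half the data, so a conventional IQR-based fence was probably meant. That may well be so, and it limits certainty about what will actually be done. It does not rescue the text. The explicit 50% wording points the other way, and nothing else in the article corrects it. An analyst who silently used a fence would depart from the published plan.

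Three further points stand as limits on the figures:

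- The rule removes data points, not whole participants. The 9.5% is the analysed sample only under listwise deletion. If all available data are used, about 89% of participants still contribute at least one visit (100% − 11.4%). The article does not fix which applies. Step 5 uses available data and the damage remains.
- The harms do not all occur together. Pooled quartiles leave the type I error near 5%, and within-arm quartiles leave the raw difference intact.
- The power figures are not this trial's operating characteristics. They use an assumed 0.5 SD effect and ignore clustering.

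**Conclusion.** The concern holds: the rule is wrong as written. It excludes about half of the valid values for each outcome, selected on the outcome, and the article offers no safe way to read it. With pooled quartiles the effect is almost erased (0.5 SD to 0.08 SD). With within-arm quartiles the type I error rises to about 30% in a two-arm test and about 59% in the five-group group-by-time test. Leaving the quartile basis open also lets the analyst choose between these outcomes.

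The loss of half the values follows from the definition alone. The other figures assume normal outcomes and no clustering, and the power figures also assume the illustrative effect. The direction does not hang on the exact effect size. This must be corrected before analysis.

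**What to change.** Delete the sentence and state that every valid value is analysed. If screening is wanted, use a fence (for example 1.5 x IQR beyond the quartiles, which flags about 0.7% of normal values) only to trigger a check against source, blinded to allocation. Exclude a value only if it is a proven recording error or impossible, and report each exclusion. For scores likely to be skewed, such as CTT times and WCST errors, a pre-specified log transform or robust sensitivity analysis deals with extreme values without deleting them. This last step is advisable but not needed to cure the defect.

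The cost is a short change of analysis-plan wording, with no additional participants and no additional data.

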**Fig. 1 Fig1:**
[figure not shown]
Flow diagram of the study through two phases of the CRCT, including recruitment, allocation, intervention, and data collections points

In each phase, four repeated assessments (T1-T4) will be conducted: T1 is the pre-test before intervention; T2 and T3 will be conducted on intervention right after the end of 2-month and 4-month, respectively; T4 is a follow-up test conducted 2 months after the completion of all intervention training. Participants of CG will be asked to assume regular-daily habitual activities and take four repeated assessments only.

The study is designed in accordance with the SPIRIT (Standard Protocol Items: Recommendations for Interventional Trials). The study protocol has been approved by University Research Ethics Committee (REC/19–20/0066) and registered at ClinicalTrials.gov Identifier: NCT04727450.

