### Outcome measures

Participants will take part in evaluation for four times, including a pre-test (T1), two post-tests (T2 and T3) at 2-month intervals, and a follow-up test (T4) two months after the intervention. The evaluators will be blind to the group membership of participants. Each evaluation includes three aspects of testing that are cognitive tests (60 min), fitness tests (30 min), and mental-related surveys (15-20 min). The total testing time per participant is less than 2 h.

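### The first analysis model uses the T1 score only as one of four outcome levels, so the arm comparisons leave precision from the pre-test unused

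*Protocol article*

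**What the plan says.** The assessment schedule gives every participant one measurement before training and three afterwards. Under Research design, "T1 is the pre-test before intervention". Under Outcome measures, "Participants will take part in evaluation for four times, including a pre-test (T1), two post-tests (T2 and T3) at 2-month intervals", followed by T4 two months after training ends.

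The first model in the Statistical analysis plan section is a mixed-effects ANOVA with five groups as the between-subjects factor and the four assessments as the within-subject factor. Its terms are listed: "The independent variables will be time (1 pre-test, 2 post-tests, and 1 follow-up) and intervention (IGs with 4 combinations of training modes & CGs". Centre enters as a random effect. No baseline covariate is named, and no constraint that the groups share a T1 mean. The section says the focus is on between-group differences, meaning those among the four intervention groups. It does not say whether that is the group main effect or the group-by-time interaction.

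The Sample size section rests on "4 trials by 5 groupings (4 IGs + 1 CG") with "parameters set to an effect size of 0.175 (small to medium") and "an alpha level of 0.05, power of 0.90, rho of 0.5".

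**The concern.** A pre-test correlated with the later scores carries information about them. How much of it reaches the arm comparison depends on where T1 sits in the model.

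- **Group-by-time reading.** The contrast is change from T1, so T1 is subtracted with its slope fixed at 1 and not at the slope the data support.
- **Group main effect reading.** T1 is averaged in with T2 to T4. Training cannot have had an effect at T1, so the average dilutes the effect and carries any chance baseline gap into the estimate.

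Precision is scarce here. There are four centres per arm, and the comparisons among intervention groups are Bonferroni-corrected. With 285/5 = 57 people per arm and the plan's ICC, the SD of the T1 difference between two arms is sqrt(2 × (0.1/4 + 0.9/57)) = 0.29 SD, so visible baseline gaps are to be expected.

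**Working it through.** **Inputs from the Sample size section:** 5 groups, 4 assessments, f = 0.175, alpha 0.05, power 0.90, rho 0.5; "It is calculated with a group size of 15 and ICC of 0.1"; "By considering a 20% of attrition rate of the participants". The stability of centre effects between visits is not given and is varied below.

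**1. The plan's own figure.** For the group-by-time interaction, lambda = N f² m/(1 − rho) = 95 × 0.175² × 4/0.5 = 23.3 on 12 and 270 df, which gives power 0.909. Then 95 × (1 + 14 × 0.1) = 228, and 228/0.8 = 285. All three figures reproduce. A between-groups test with the same inputs would need 320 and has power 0.35 at 95, so 95 belongs to the interaction.

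**2. Contrast variance, independent participants** (sigma² = 1, equal correlation 0.5, r post-training visits):

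- Unadjusted post mean: (1 + (r − 1)rho)/r
- Change from T1: post mean + 1 − 2 rho
- Adjusted for T1: post mean − rho²
- Four-visit group mean, rescaled for dilution (r = 3): ((1 + 3 rho)/4)/(3/4)² = 0.625/0.5625 = 1.111

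| | Post | Change | Adjusted | Saving |
|---|---|---|---|---|
| Mean of T2–T4 | 0.667 | 0.667 | 0.417 | 37.5% |
| One visit | 1.00 | 1.00 | 0.75 | 25% |

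Against the four-visit group main effect the saving is 1 − 0.417/1.111 = 62.5%.

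**3. The same at centre-mean level** (ICC 0.1, 15 per centre). Let c be the correlation of a centre's effect between visits. Person-level covariance is p = 0.5 − 0.1c. A centre mean has variance V = 0.1 + 0.9/15 = 0.16 and between-visit covariance C = 0.1c + p/15. Over T2 to T4: post = C + (V − C)/3, change = (V − C) × 4/3, adjusted = post − C²/V.

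For c = 1: C = 0.1267, C/V = 0.79, post = 0.1378, change = 0.0444, adjusted = 0.0375. The saving against change is 15.6%.

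| c | Saving vs change, T2–T4 | Saving vs change, one visit | Saving vs four-visit main effect |
|---|---|---|---|
| 1 | 15.6% | 10.4% | 84% |
| 0.8 | 24% | 16% | 76% |
| 0.5 | 37.5% | 25% | 62.5% |
| 0 | 59% | 40% | 41% |

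**4. Individual T1 as the only covariate.** With a random centre effect, its slope is estimated mostly within centres, about 0.4/0.9 = 0.444 at c = 1, whereas centre means need 0.79. The centre-mean variance becomes 0.1378 − 2 × 0.444 × 0.1267 + 0.444² × 0.16 = 0.0568, which is 28% above change (0.0444). Two simulations of the fitted model under these settings gave arm-difference variances of 0.0273 against 0.0221 (24% higher) and 0.0288 against 0.0228 (26% higher). Adding the centre-mean T1 brought these to 0.0200 and 0.0209, about 8% to 10% below change.

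**The case against.** A group-by-time mixed ANOVA with T1 as a response is a standard and valid analysis. The test that N = 95 was sized for already uses T1, and the sample size claimed no gain from adjustment. Lists of covariates are often left to a full analysis plan. And 37.5% assumes that centre effects correlate only 0.5 between visits, whereas a random centre effect in its simplest form is fully stable and cancels in change scores.

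Most of this stands. It limits the point to efficiency and removes 37.5% as a general figure. It does not remove the point: the article does not leave the terms open but lists them, and in the calculation above adjustment saves variance at every centre autocorrelation checked.

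Four stronger readings do not hold:

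- **That the analysis is invalid, or that 285 is too few.** Nothing here shows either. The sample size reproduces for the interaction.
- **That power would rise from 33% to 51%.** Those figures apply f = 0.175 to a five-arm comparison of T2 to T4 means with a constant effect. The plan did not size that test, and the two-mode arms change mode after two months. They are illustrative at most.
- **That adding each person's T1 score must narrow the intervals.** With stable centre effects it widens them relative to change scores.
- **That half of any baseline gap enters a change comparison with opposite sign.** With stable centre effects the expected share is about 1 − 0.79 = 0.21.

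**Conclusion.** The point holds as an efficiency improvement. The first model uses T1 inefficiently under the interaction reading, and lets it dilute the comparison under the main-effect reading. Against change scores over T2 to T4, the variance saving at the plan's ICC and rho is about 16% with fully stable centre effects, 24% at autocorrelation 0.8, and 37.5% only at 0.5. Against the four-visit group main effect it is 41% to 84% over the whole range checked.

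These figures assume equal correlation of 0.5 between visits, 15 per centre and known covariances. With 20 centres the covariances must be estimated, so the realised gain will be smaller: with stable centre effects, the simulated gain for the two-covariate form was 8% to 10%, not 15.6%. The equal-baseline form was not simulated. Both forms also assume that the arms are comparable at T1 in expectation. The Interventions section describes centres being assigned and asked to recruit, so the order of allocation and recruitment should be confirmed.

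**What to change.** In the first model, keep T1 as a response but constrain the group means to be equal at T1. Include random effects for centre and for person, and for centre-by-time if centre effects are not stable. Report group differences at the post-training visits, so that the between-group focus has a defined contrast. This form keeps people with no T1 score.

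Alternatively, take T2 to T4 as the responses, with both the individual T1 score and the centre-mean T1 score of the same outcome as covariates. Do not use the individual score alone.

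The cost is a short change to the analysis text, with no new data, visits or participants. Statistically it is one or two degrees of freedom per outcome. For the centre-mean term these are between-centre degrees of freedom, of which five arms and 20 centres leave only 20 − 5 = 15. The covariate form also loses people with no T1 score.

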## Methods

### Research design

This study is a cluster randomized controlled trial (CRCT), to be carried out in 20 community elderly centres (see Fig. 1). The elderly centres will be randomly selected from the population list of elderly service providers in the 18 districts of Hong Kong and assigned to either one of the 4 Intervention Groups (IGs) or the Control Group (CG). There will be 16 centres in the IGs and 4 centres in the CG participating in a 6-months program (4-month intervention with 2-month follow-up). The 20 participating centres will be equally allocated to two Phases, I and II, with each Phase involving 8 centres in IGs and 2 centres in CG. Each IG will be randomly assigned to one of the four combinations of three training modes that include cognitive (A), physical (B), and combined cognitive and physical training (CCPT, i.e. C), namely Mixed ABC, A + B, C + A, B + C. The intervention will last for 4 months in which the training is conducted for 16 sessions, 2 sessions per week, and 60 min per session.

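### If centre is fitted as a single random intercept, the group-by-time test on which the trial was sized gets no adjustment for clustering

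*Protocol article*

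**What the plan says.** Statistical analysis plan section: the model has a between-subjects factor of five groups and "a within-subject factor consisting of four Trials (Time = 1 to 4"). On clustering there is one sentence: "The participating elderly centre as a cluster will be treated as a random effect". The section does not say whether this means an intercept alone or also a centre-by-time effect. It puts the focus mainly on between-group differences among the intervention groups and does not name group-by-time as the test of programme effect. A second model, for the three training modes, is described as similar.

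Sample size section: the unclustered n comes from "repeated measures of ANOVA analyses of 4 trials by 5 groupings (4 IGs + 1 CG"), with "an effect size of 0.175 (small to medium), an alpha level of 0.05, power of 0.90, rho of 0.5". It is then inflated by a design effect: "It is calculated with a group size of 15 and ICC of 0.1", which gives 2.4. The result is "The required sample size for a CRCT is 228", raised to 285 for 20% attrition.

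Research design section: "There will be 16 centres in the IGs and 4 centres in the CG", that is, four centres in each of the five arms if the 16 are divided equally among the four programmes, as the Interventions section indicates.

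**The concern.** A centre effect that is constant from T1 to T4 is subtracted away in every change from T1, and therefore in every group-by-time contrast. If it is the only centre term, those contrasts are judged against pooled participant-level variation with several hundred degrees of freedom, although only 20 centres were randomised. When centres of the same arm differ in how much their members change, that error term is too small.

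Such differences are plausible. Training is delivered to whole centres, and the centres run in two phases. For the board games, the instructor and assistant are recruited from the centre itself.

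At stake are the p-values and confidence intervals for change, the quantity that would show a training effect. A programme could be declared effective because a few of its four centres happened to improve.

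**Working it through.** **1. Which test was powered.** Inputs from the Sample size section: f = 0.175, alpha = 0.05, power 0.90, rho = 0.5, k = 5 groups, m = 4 times. Noncentral F, sphericity assumed.

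- Group-by-time: lambda = f² × N × m / (1 − rho) = 0.030625 × 95 × 4 / 0.5 = 23.3, with (k − 1)(m − 1) = 12 and (N − k)(m − 1) = 270 df. Power is 0.909, and the smallest multiple of 5 that reaches 0.90 is 95.
- Group main effect: lambda = f² × N × m / (1 + (m − 1) × rho) = 0.030625 × 95 × 4 / 2.5 = 4.66, with 4 and 90 df. Power is 0.35, and 320 would be needed.
- Time main effect: 60 would be enough.

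Only group-by-time gives 95. The rest of the chain also reproduces: 1 + 14 × 0.1 = 2.4; 95 × 2.4 = 228; 228 / 0.8 = 285. The plan therefore inflates a group-by-time sample size for clustering.

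**2. What a centre intercept does.** On one simulated balanced data set (20 centres, 14 per centre), adding a very large centre intercept left the group-by-time F against participant-level error unchanged at 3.196. The group main-effect F, tested against centres, moved from 1.49 to 1.03. Against centre-by-time error, the same group-by-time F was 1.34. So the intercept carries clustering into the group main effect and none into group-by-time.

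**3. Size of the effect.** *Assumption:* the ICC of change (centre-by-time variance divided by centre-by-time plus residual variance) is not in the documents, so a range from 0 to 0.10 is shown. Other inputs: 20 centres, 4 per arm, and n = 228 / 20 = 11.4 analysed per centre, all taken as equal in size. Let b = 1 + n × ICC / (1 − ICC).

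- The group-by-time mean square is distributed as b × chi-square(12) / 12.
- The pooled error mixes b × chi-square on 5 × (4 − 1) × 3 = 45 df with chi-square on (228 − 20) × 3 = 624 df, 669 df in all.
- The statistic is referred to F(12, 669). Rejection rates come from 400,000 draws.

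| ICC of change | b | 12-df test | 1-df contrast | 12-df test against centre-by-time |
|---|---|---|---|---|
| 0 | 1.00 | 0.05 | 0.05 | 0.05 |
| 0.01 | 1.12 | 0.09 | 0.06 | 0.05 |
| 0.02 | 1.23 | 0.14 | 0.075 | 0.05 |
| 0.04 | 1.48 | 0.25 | 0.10 | 0.05 |
| 0.10 | 2.27 | 0.60 | 0.17 | 0.05 |

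With all 285 analysed (14.25 per centre), the 12-df figure at an ICC of change of 0.10 is 0.71 and the 1-df figure 0.20.

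**4. Power after the change.** At an ICC of change of 0.10 and 228 analysed, lambda = 0.030625 × 228 × 4 / 0.5 / (1 + 10.4 × 0.1) = 55.86 / 2.04 = 27.4. With 12 and 45 df, power is 0.903. With 285 it is 0.93.

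**The case against.** The strongest reply is that the sentence on centre is open. It does not say intercept, and it does not exclude a centre-by-time term. In a classical mixed ANOVA, a random centre factor nested in group and crossed with time makes centre-by-time the error term for group-by-time, which is the correct test. The article is a condensed account, and such detail may stand in a fuller plan. This stands in part: the wording permits the correct model. But the plain reading is one centre effect, and the two readings lead to very different error rates for the effect that was powered.

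A reader might infer three stronger things that the documents do not support.

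- *That the analysis ignores clustering altogether.* The stated focus is on between-group differences. If that means the group main effect, even an intercept carries the clustering there. The mismatch is then with the sample size: that effect has power 0.35 at the unclustered n of 95.
- *That 0.60 is the expected error rate.* The ICC of 0.1 comes from an earlier study and is never said to be an ICC of change. If the ICC of change is zero, there is no inflation. The 0.60 is the upper end of an assumed range, and single contrasts are affected much less.
- *That all training is given by centre-specific instructors.* This is stated only for the board games. Line-dance instructors come from associations or through media, combined-training leaders follow a manual, and first sessions are observed in every mode.

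**Conclusion.** The concern holds conditionally. The plan does not fix the random-effects structure or name the test of programme effect. If centre enters as a random intercept only, the powered group-by-time test receives none of the clustering adjustment that the design effect of 2.4 was meant to cover. An ICC of change of only 0.01 to 0.02 would take the 12-df test from 5% to about 9% to 14%; 0.10 would take it to about 60%. For one contrast the range is 5% to 17%. These figures assume 20 equal centres of 11.4 analysed, sphericity, and an ICC of change that the documents do not supply. They do not apply to the group main effect, or to a model in which centre is already crossed with time.

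**What to change.** Name group-by-time as the test of programme effect, to match the Sample size section. Write the model as fixed group, time and group × time, with random centre, random centre × time and random participant within centre, and use Satterthwaite or Kenward-Roger degrees of freedom. These are about 45 for group-by-time if centres are balanced, and fewer if phase is also modelled. Use the same structure in the second model. An analysis of centre means at each occasion is equivalent only when centres are of equal size, which attrition makes unlikely.

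The cost is a sentence or two of wording and wider intervals where centres do differ in change. From the expected mean squares above, the standard error of a contrast grows by a factor of √(b × 669 / (45b + 624)): about 1.10 at an ICC of change of 0.02 and 1.45 at 0.10. No new data are needed. Power for the interaction stays about 0.90 with 228 analysed, even at 0.10.
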